#### Molecular assays

DBS collected onto filter paper cards (Whatman® 903 Protein Saver, Sigma-Aldrich) will be allowed to rack-dry overnight and stored individually in opaque sealable plastic bags with desiccant before subsequent use in PCR assays. PCR detection of parasites will be done using cytochrome b. Recurrent episodes will be genotyped to distinguish recrudescence infections from new infections according to standard WHO protocols will be conducted with nested PCR of *merozoite surface protein-1* and -*2* (*msp1*, *msp2*) and glutamate-rich protein (*glurp*) genes for length polymorphisms [22]. Infections will be classified as recrudescent infection if, for each marker, there is at least one identical allele between the initial and recurrent infection. Infections will be classified as reinfections if, for at least one marker, there is a different length polymorphism between the initial and recurrent infection. Infections will be classified as indeterminate in the case of low coverage or missingness due to amplification failure that precludes comparisons at all three genes. Drug resistance markers for artemisinins, SP, piperaquine, and related markers for chloroquine and amodiaquine cross-resistance will be evaluated by molecular inversion probe and amplicon deep sequencing based approaches [23, 24].

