### Statistical analysis {20a} {20b} {20c}

Longitudinal data will be displayed using the nonparametric Kaplan-Meier estimations of the survival function. The primary analysis will be comparison of the 42-day incidence of MIP using multivariate models to estimate the relative hazard between the IPTp-SP and IPTp-SP+ groups according to intention-to-treat (ITT). Testing for proportionality of hazards will be done using formal statistical testing with Schoenfeld residuals as well as visual inspection of the nonparametric survival estimates. For non-proportional hazards, an extended Cox model will be applied. To handle interval censoring due to participants who miss one or more follow-up visits, we will use parametric models for interval-censored survival-time data. The relative hazard will be estimated in parametric models accounting for recurrent events by using a robust variance estimator. For the primary safety analysis, we will compare the proportions of serious and non-serious AEs using logistic regression models and relative hazards of AEs using Cox regression methods as above. Secondary analyses of continuous outcomes (hemoglobin concentration, birthweight) will be examined in linear regression models and in logistic regression models for binary outcomes (prevalence of low birth weight, neonatal mortality, placental malaria, congenital malaria, maternal anemia, congenital anemia, drug resistance allele frequency). Prespecified subgroup analyses will be done according to the following strata: primigravidae, multigravidae, gestational age at enrollment, delivery before or after the day 63 visit, treatment dose on a mg/kg basis, positive *P. falciparum* PCR on enrollment, and presence or absence of quintuple and sextuple mutations. In a secondary analysis, we will compare the proportions of treatment failures and prevention failures according to the antimalarial drug given at the first encounter (SP or DP) in an on-treatment analysis using logistic regression. Treatment failures will be defined as recurrent infections that are determined by genotyping to be recrudescent parasites from the initial infection in participants who tested positive by PCR at the initial visit. Prevention failures will be defined as PCR-confirmed parasitemia in participants who initially tested negative by PCR at the first visit, or who tested positive by PCR at the first visit but who experienced reinfection with a new parasite as determined by genotyping. No interim analysis is planned. Every effort will be made to collect complete data for all participants and minimize missing data. Missing data will be handled using multiple imputation.

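### The recrudescence and reinfection rules overlap for multi-allele samples, so some recurrences in women PCR-positive at entry can count as treatment failure, prevention failure or both

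*Protocol article*

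**What the plan says.** The protocol article, under Molecular assays, types recurrences at msp1, msp2 and glurp and gives three classes.

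- Recrudescence: "Infections will be classified as recrudescent infection if, for each marker, there is at least one identical allele between the initial and recurrent infection".
- Reinfection: "Infections will be classified as reinfections if, for at least one marker, there is a different length polymorphism between the initial and recurrent infection".
- Indeterminate: "Infections will be classified as indeterminate in the case of low coverage or missingness due to amplification failure that precludes comparisons at all three genes".

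The section cites an outside standard ("Recurrent episodes will be genotyped to distinguish recrudescence infections from new infections according to standard WHO protocols") but writes out these rules itself. It gives no order of precedence and no mixed class.

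Statistical analysis builds two outcomes on these calls. The first reads "Treatment failures will be defined as recurrent infections that are determined by genotyping to be recrudescent parasites from the initial infection", in women PCR-positive at the initial visit. The second has two branches: "Prevention failures will be defined as PCR-confirmed parasitemia in participants who initially tested negative by PCR at the first visit", which needs no genotyping, and "or who tested positive by PCR at the first visit but who experienced reinfection with a new parasite as determined by genotyping", which does. The two outcomes are compared by first drug (SP or DP) in a secondary on-treatment analysis. Table 1 lists treatment or prevention failure at day 42 by drug under the primary objectives, but does not mark it as a primary outcome.

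**The concern.** Recrudescence asks for one match at every marker. Reinfection asks for one difference at any marker. A match and a difference exclude each other only when both samples carry a single allele at the marker. With several alleles, one marker can show both at once, and the text does not say which rule then wins. The indeterminate class does not help, because it covers assay failure only.

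At stake is how recurrences are divided between failure to clear the initial infection and failure to prevent a new one, and so how SP and DP are contrasted on each. Two laboratories or analysts could apply the printed rules faithfully and report different counts.

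**Working it through.** **Step 1, the logic.** Let S0 and S1 be the sets of alleles at one marker in the initial and the recurrent sample.

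- Recrudescence: S0 and S1 share an allele at all three markers.
- Its complement: S0 and S1 share no allele at one or more markers.
- Reinfection, broad reading: S0 and S1 differ in any way at one or more markers.
- Reinfection, narrow reading: S1 holds an allele absent from S0 at one or more markers.

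Both readings are weaker than the complement. Every fully typed pair that fails recrudescence is a reinfection, so there is no gap. The reverse does not hold, so there is an overlap.

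**Step 2, constructed profiles.**

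| Initial (msp1; msp2; glurp) | Recurrent | Recrudescence rule | Reinfection rule |
|---|---|---|---|
| {a}; {b}; {c} | {a}; {b}; {c} | met | not met |
| {a}; {b}; {c} | {a}; {d}; {c} | not met | met |
| {a}; {b}; {c} | {a}; {b,d}; {c} | met | met, both readings |
| {a}; {b,d}; {c} | {a}; {b}; {c} | met | met, broad reading only |
| {a}; {b,e}; {c} | {a}; {d}; {c} | not met | met |

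Rows 3 and 4 are the problem. Row 5 shows that a polyclonal pair can still be classified cleanly.

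**Step 3, who is exposed.** Only women PCR-positive at the first visit depend on genotyping. The Sample size section cites 22–26% prevalence from prior studies in the same population. Applying that range to the trial is an assumption.

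- Recruited: 0.22 × 392 = 86.2 and 0.26 × 392 = 101.9, so about 86–102 women.
- Evaluable: 0.22 × 324 = 71.3 and 0.26 × 324 = 84.2, so about 71–84 women.

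Only those among them who have a recurrence can be ambiguous. The other 74–78% need no genotyping call.

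**Step 4, how often both rules are met.** The document gives no clone multiplicity, allele frequencies or share of recrudescence, so this is a range under assumptions. Clone counts were simulated as zero-truncated Poisson with means of about 1.6, 2.0 and 3.0. Alleles were equally common, at 5/8/5 or 10/15/10 per marker. Each scenario had up to 8,000 pairs, keeping those with at least one polyclonal sample.

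| Assumed truth | Both rules met, broad reading | Both rules met, narrow reading |
|---|---|---|
| Recrudescence only | 54–66% | 0% |
| Recrudescence plus a new clone | 99.2–99.9% | 97.5–99.8% |
| Reinfection only | 2.5–41% | 2–38% |

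The overall share depends on the mix of the three rows, which is unknown.

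**Step 5, effect on the comparison.** For drug d, let n be the denominator, T the recurrences meeting only the recrudescence rule, P those counted only as prevention failure, and B those meeting both rules. The treatment failure proportion lies between T/n and (T + B)/n. The prevention failure proportion lies between P/n and (P + B)/n. Moving the overlap in or out shifts the SP minus DP difference by B/n for SP minus B/n for DP. The sign of that shift is not known in advance.

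**Step 6, after the change.** If reinfection requires no shared allele at one or more markers, it is the exact complement of recrudescence. Overlap is 0% by construction, and every pair typed at all three markers gets one class. Exclusive does not mean accurate: in Step 4, 2.5–41% of polyclonal reinfections share an allele at every marker by chance and would be called recrudescent. Most of these also carry a new allele (2–38% of polyclonal reinfections), so a mixed flag would pick them out.

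**The case against.** Four arguments weigh against the point.

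1. The article cites standard WHO protocols, and the two sentences may be meant as complements: all markers match, or at least one does not. That may be the intention, but the cited text is not shown and the printed rule says something else. This is a stated rule that conflicts with its neighbour, not a detail left to another document.

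2. The statistical section speaks of a new parasite, which favours the narrow reading. This stands. Loss of a clone alone would then not count as reinfection, and the overlap for pure recrudescence falls to 0%. Recrudescence with an added clone still meets both rules on either reading.

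3. A woman in whom an old clone persists and a new one appears has had both events, and nothing says the two failures must be exclusive. Counting her in both proportions is coherent. It would have to be stated, and under the broad reading it would also double-count women who merely lost a clone.

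4. The affected analysis is secondary. This stands and sets the severity. If the Table 1 entry is read as one combined outcome, the class makes no difference to it.

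**Conclusion.** The rule is wrong as written, with minor to moderate consequences. The two definitions are not mutually exclusive for samples with more than one allele at a marker, and nothing in the article resolves a recurrence that meets both. The ambiguity is confined to recurrences among women PCR-positive at entry, and its size cannot be derived from the document. The primary outcome is infection by PCR at day 42 and needs no genotyping, so that outcome and the sample size stand.

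Two stronger inferences are tempting and are not supported. A reader might infer that most polyclonal recurrences meet both rules. With 10 equally common alleles per marker, two initial clones and one retained, overlap is indeed 1 − (1/10)^3 = 0.999. But that conditions on a true recrudescence with a lost clone, and it disappears under the narrow reading. Polyclonal pure reinfections mostly meet one rule only. A reader might also infer that treatment failure and prevention failure cannot be separated at all. Single-clone pairs, pairs with no shared allele at some marker, and all women PCR-negative at entry are classified without ambiguity.

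**What to change.** Keep the recrudescence rule. Restate reinfection as: for at least one marker, no allele is shared between the initial and recurrent infection. Flag recurrences with shared alleles at all markers plus additional alleles as mixed (recrudescence plus new infection). Count them as recrudescence in the main version of this secondary analysis, and add a sensitivity analysis that also counts them as prevention failures.

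The cost is one sentence in the genotyping definition, its copy in the laboratory procedure, and one sensitivity analysis. No new assays are needed, and any pairs already called can be reclassified from their recorded alleles. The change should be made and dated before unmasking. Trial status reports that data collection is still ongoing, and the masking section keeps statisticians and outcome assessors masked until database lock. Because investigators are unmasked earlier, once all participants have delivered, the rule should be settled by the staff who are still masked.

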#### Plasma piperaquine concentrations

Participants who are randomized to the IPTp-SP+ who screen positive and are administered DP treatment will have an additional 2 mL blood collection for measurement of piperaquine plasma concentrations on days 0, 14, 28, 35, and 42. Piperaquine quantitation will be done using liquid chromatography tandem mass spectrometry as previously described [25]. The terminal elimination half-life will be estimated using noncompartmental analysis, and the effect of age, body surface area, body mass index, and gestational age on drug concentrations will be explored in mixed effects models using WinNonlin software (Certara, Princeton, NJ).

#### Biological specimen storage

Blood slides will be stored in slide boxes. DBS samples will be packaged in zip-lock polythene bags with desiccant and stored and transported in boxes. Placental tissues will be packed in containers with formalin. Samples from study clinics will be taken to the satellite TDRC laboratory in Nchelenge where they will be stored temporarily before shipment to TDRC in Ndola for long-term storage. For participants who consent to future use of specimens, after a 10-year storage period all samples will be destroyed following TDRC standard operating procedures. Biological specimens from participants who do not consent for future use will be destroyed immediately after laboratory analysis. Access to samples by TDRC researchers during the study will be done through the principal investigator, and after the study is completed, it will be done through TDRC management.

### Safety assessments {22}

Drug safety will be monitored at every visit during the course of the study in compliance with International Conference on Harmonization Good Clinical Practice guidelines for adverse events (AEs) and serious adverse events (SAEs) [26]. All expected and unexpected AEs will be collected and reported in trial publications. SAEs will be reported to the sponsor and the ethics committee within 24 working hours of the study staff first becoming aware. Investigators will determine the relationship between safety signals and the study drugs and define outcomes, according to standard classifications [26].

### Sample size calculation {14}

The sample size was determined based on available data and with the objective of achieving a detectable difference of a 50% reduction in the incidence of MIP. In 2019, Nchelenge District recorded 7791 live births (unpublished data). Prior studies in the same population found PCR prevalence of *P. falciparum* parasitemia to be 22–26% in pregnant women [14, 15]. A sample size of 324 pregnant women (*n*=162 per arm) will afford 80% power to detect a 50% difference of effect between study arms with a two-tailed alpha of 0.05. To allow for loss to follow-up of up to 20%, a total of 392 (*n*=196 per arm) will be recruited.

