### Randomization and masking {16a} {16b} {16c} {17a} {17b} {23}

The following procedures will be used to ensure an unbiased assessment of treatment safety and efficacy. A computer-generated randomization schedule will be generated by the study statistician prior to the start of the study and kept in a locked cabinet accessible only to the study coordinator who will be responsible for assigning participants to a study treatment arm. The schedule will comprise blocks of varying size to allocate, in a 1:1 ratio, eligible participants to either IPTp-SP or IPTp-SP+. The trial is open-label. However, study investigators, study clinicians, and statisticians are masked to treatment assignment. Investigators will be unmasked after all participants have delivered. A Data and Safety Monitoring Board (DSMB) will be established to review safety data. Statisticians will remain masked until after the DSMB has approved the final analysis plan and the database is locked. All outcome assessors, including laboratory parasitologists and pathologists, will also be masked until the final database is locked.

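### Recruiting 392 women keeps the required 324 only with loss up to about 17%, not the stated 20%

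*Protocol article*

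**What the plan says.** All the relevant figures are in the protocol article under Sample size calculation {14}. The aim is given as "with the objective of achieving a detectable difference of a 50% reduction in the incidence of MIP". The evaluable requirement is "A sample size of 324 pregnant women", that is, "162 per arm) will afford 80% power". The target is worded as "80% power to detect a 50% difference of effect between study arms with a two-tailed alpha of 0.05".

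The recruitment figure follows: "To allow for loss to follow-up of up to 20%, a total of 392", with "196 per arm) will be recruited".

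The only rate offered as background is from earlier work in the same population, which found PCR-detected "parasitemia to be 22–26% in pregnant women". The section does not say which single control-arm rate produced 162 per arm. Allocation is 1:1 (Randomization and masking). No other section gives a different loss rate or another rule for inflating the sample.

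**The concern.** An allowance for loss has a simple test: apply the stated loss to the recruited number and see whether the required number remains. Here it does not. Three figures given together (324 needed, 20% loss, 392 recruited) cannot all be right.

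This is the only sample-size justification in the article. A reader judging the completed trial will take attrition of 18–20% as planned for, when it would leave the trial below its own evaluable target. What is at stake is the accuracy of the stated loss tolerance and, to a small degree, the power that goes with it.

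**Working it through.** **Inputs** (Sample size calculation {14}, with the 1:1 ratio from Randomization and masking): evaluable 324, or 162 per arm; recruited 392, or 196 per arm; loss up to 20%; power 80%; two-sided alpha 0.05; 50% relative reduction; background prevalence 22–26%.

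**1. The base figure of 162 per arm.** The usual two-proportion formula with pooled variance under the null is

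n = [1.96·√(2·p̄·(1−p̄)) + 0.8416·√(p₁(1−p₁) + p₂(1−p₂))]² / (p₁−p₂)², with p₂ = p₁/2 and p̄ the mean of the two.

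At p₁ = 24%, p₂ = 12%, p̄ = 18%: [1.96·√0.2952 + 0.8416·√0.288]² / 0.12² = 2.300 / 0.0144 ≈ 160 per arm. At 22% it gives 178, at 25% 152 and at 26% 145. With a continuity correction, 26% gives 160. So 162 is close to what a rate near 24% yields, but a different rate and formula come equally close. The 24% used below is an assumption (the midpoint of the cited range), not a figure from the protocol.

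**2. The loss allowance.** This step needs no assumption about the control rate.

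- Evaluable after 20% loss: 392 × 0.80 = 313.6, about 314. Per arm: 196 × 0.80 = 156.8, about 157.
- Shortfall: 324 − 313.6 = 10.4, about 10 women, or about 5 per arm.
- Largest loss that keeps 324: 1 − 324/392 = 17.3%.
- Recruitment needed for 20% loss: 324/0.80 = 405. Per arm 162/0.80 = 202.5, rounded up to 203, so 406 with equal arms. That is 13–14 more than 392.

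**3. How 392 may have arisen.** 392/324 = 1.21. Multiplying by 1.2 gives 324 × 1.2 = 388.8, or 162 × 1.2 = 194.4 (195 per arm, 390 in total). This is close to 392 but not equal to it. Multiplication where division was needed is a plausible cause, but it remains a conjecture.

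**4. What the shortfall costs in power.** Assume that the cited prevalence is the control-arm day-42 risk and that women lost contribute nothing. With the same formula,

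power = Φ{[(p₁−p₂)·√n − 1.96·√(2·p̄·(1−p̄))] / √(p₁(1−p₁) + p₂(1−p₂))}.

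| Assumed control risk | Halved risk | Power, 162 per arm | Power, 157 per arm | Difference (points) |
|---|---|---|---|---|
| 22% | 11% | 76.3% | 75.0% | 1.3 |
| 24% | 12% | 80.6% | 79.3% | 1.3 |
| 26% | 13% | 84.3% | 83.2% | 1.1 |

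Under these assumptions 162 per arm reaches 80% from a control risk of about 23.7% upward, and 157 per arm from about 24.3% upward.

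**The case against.** The strongest reply is that the shortfall may not be a real loss of information. Under Statistical analysis, the primary comparison is an intention-to-treat relative hazard, with interval-censored models for missed visits and multiple imputation for missing data. Visits fall on days 14, 28, 35 and 42, so a woman lost before day 42 may still contribute. A two-proportion formula that discards her is only an approximation and may overstate the cost. This stands as a limit on the power figures. It does not rescue the sentence, because the section sets its own requirement of 324 and makes its own allowance for loss, and the two disagree whatever model is used later.

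It is also fair to say that the error is small, that 20% is a ceiling and not a forecast, and that recruitment ended on 19 June 2020 (Trial status), so the design cannot change. All of that stands, and it sets the severity.

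A reader might go further and infer that 80% power holds only at a control risk near 24% and fails over the rest of the 22–26% range. The documents do not support that. On the assumptions above, 162 per arm gives at least 80% at every rate from about 23.7% upward, including 84% at 26%; only the lower part of the range falls short. The section does not claim 80% power across the whole range either. It cites a prevalence as background and names no design rate.

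**Conclusion.** The loss allowance is wrong as written. With 392 recruited, the required 324 remain only if loss is at most about 17%. A 20% loss leaves about 314 women, 157 per arm, and covering it would have taken 405–406. This conclusion rests only on figures in the sample size section.

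The consequence is minor: about 1.1–1.3 percentage points of power if loss reaches the full 20%. That size rests on three assumptions: that the 22–26% prevalence stands for the control-arm day-42 risk, that a two-proportion comparison approximates the planned hazard analysis, and that women lost add no information. A reader might infer that the trial is materially underpowered because of this slip; an effect of this size does not support that. The choice of control rate matters more than the loss error: under the same assumptions, power at 162 per arm runs from 76% at 22% to 84% at 26%.

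**What to change.** Correct one sentence in Sample size calculation {14}; no more women are needed. Either of these would do:

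- state that recruiting 392 women (196 per arm) keeps 324 evaluable with loss to follow-up of up to about 17%; or
- keep the 20% ceiling and state that it would leave about 157 per arm, at a cost of about 1 percentage point of power.

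If power figures are added, the control rate and formula actually used to obtain 162 per arm should be given with them. The 24% used here should not be put into the text as though it were the design value.

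The cost is one sentence and a slightly less favourable stated tolerance. Design, conduct and analysis are unaffected. Data collection was still under way according to Trial status, so the correction could be carried into the reporting of results.
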